### Demographics and clinical characteristics

At T1 the following data will be recorded: participant age, gender, cancer type and stage, time since diagnosis, PCOC status, type of referral to the study (e.g. medical practitioner, media, word of mouth), symptoms, types of treatment and side effects, relevant allied health management and other existing medical conditions if applicable. We will also record height, weight, body mass index (BMI), resting heart rate and blood pressure.

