**Assessments / Tools**							
Demographics & Clinical Characteristics			X				
Physical Function (Resting HR, BP, O2sat, 6MWT, 30-s Sit-to-Stand)			X	X	X		
Health-related Quality of Life (EORTC QLQ-30) questionnaire			X	X	X	X	
Anxiety & Depression (HADS) questionnaire			X	X	X	X	
General Physical Activity (IPAQ-SF)			X	X	X	X	
Dietary Intake (MEDAS) questionnaire			X	X	X	X	
Mood (Daylio app)			X	X	X	X	
Sleep Quality (Daylio app)			X	X	X	X	
Participant Satisfaction, Diet, Exercise behaviour, Intent Feedback Surveys					X	X	
Parkrun event Adherence					X	X	
INTERVENTIONS:							
Parkrun participation					X		

This protocol describes a single group cohort study with participants acting as their own controls [23]. The study outline and timeline is shown in Fig. 1.

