### Inclusion criteria

Cancer survivors, aged 18 years or over, diagnosed with any type of cancer (e.g. breast, prostate, colorectal, blood, bone), who have medical clearance to walk and exercise, are eligible for the study. “Cancer survivor” is described as undergoing medical treatment or in remission. Participants would be classified according to the Palliative Care Outcomes Classification (PCOC); either Stage 1 (stable) or Stage 2 (unstable but not deteriorating) [24]. Participants must have given informed consent and must be registered with parkrun before start of the first walk/run event. Participants must be able to understand and communicate in English or participate with a carer/support person who can communicate in English. Finally, participants must be able to commit to the 9-month period of the study.

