### Intervention

The study has a participant time commitment of 9 months, which includes 1 month of normal activities and management to establish baseline values for outcome measures, followed by 6 months of parkrun participation, and then a follow up at 2 months post-intervention. During the 6 months of parkrun, participants can complete events at their discretion. Parkrun events occur each Saturday morning but we anticipate that many participants may not be able to join in on a weekly basis due to cancer treatment cycles, symptoms, family or work commitments or poor weather. Parkrun events start at approximately 7am, and participants can walk or jog at their own pace. There is no set finish time but the events are normally completed within 2 h, allowing social gathering time afterwards.Volunteer marshals are stationed every few hundred metres along the paths to assist with directions, encouragement and for participant safety. Each participant wears their individual barcode so that their finish time is recorded electronically, captured and stored by the parkrun organisation. Individual results can be accessed by each participant.Volunteers have first aid and CPR training.Each course will have a first aid kit and automated defibrillator available and access for emergency vehicles if necessary.In the case of bad weather, an event would be cancelled.

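### Treatment, clinically recorded side effects and PCOC status are scheduled at T1 only, so later changes in treatment status cannot be adjusted for when change from baseline is interpreted

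*Protocol article*

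**What the plan says.** Under Demographics and clinical characteristics the protocol article states: "At T1 the following data will be recorded: participant age, gender, cancer type and stage, time since diagnosis, PCOC status". The same list goes on to "symptoms, types of treatment and side effects, relevant allied health management and other existing medical conditions if applicable". Table 1 agrees. Its row "Demographics & Clinical Characteristics" carries a single mark, in the baseline column, whereas quality of life, anxiety and depression, general activity and diet are marked at all four time points.

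Four other statements bear on this:

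- **Design (text below Table 1):** "This protocol describes a single group cohort study with participants acting as their own controls".
- **Inclusion criteria:** a cancer survivor "is described as undergoing medical treatment or in remission", in PCOC stage 1 or 2. The expected mix is not given.
- **Intervention:** "1 month of normal activities and management to establish baseline values for outcome measures, followed by 6 months of parkrun participation". The section also anticipates that "many participants may not be able to join in on a weekly basis due to cancer treatment cycles, symptoms, family or work commitments".
- **Study objectives:** acceptability and adherence are primary and efficacy is secondary. One hypothesis is that physical function, quality of life, mental health, symptoms and side effects will be better than at baseline.

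The sample size rests on the proportion meeting activity guidelines, taken as 30% on average.

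**The concern.** Over a nine-month commitment some participants will probably finish treatment, and others may start or change it. The Background section lists treatments and side effects among the reasons for low exercise participation, and the Intervention section expects treatment cycles to affect attendance. Treatment status can therefore move both the exposure (events attended) and the outcomes (activity, function, quality of life, side effects).

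In a single group compared with its own baseline, improvement after treatment ends adds to the change seen at T3. With status recorded only at T1, the analyst cannot tell whose status changed. No later analysis plan can adjust for a variable that was not collected.

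At stake are the secondary efficacy results and the activity outcome that set the sample size. The hypothesis on side effects is the most exposed, because the clinical record of side effects is itself scheduled once.

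**Working it through.** **1. Is this a stated schedule or an omission?** The text and Table 1 both place these items at T1, and neither lists them at T2, T3 or T4. It is therefore a stated collection choice, not detail that a condensed article leaves out.

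**2. Could another planned source supply status over time?**

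- The quality-of-life questionnaire (T1–T4) may reflect symptoms, but as an outcome.
- Individual follow-up after missed events or attrition (Statistical analyses section) may reveal treatment, but a regular attender who finished treatment would not be asked.
- The T3 and T4 surveys ask about barriers to involvement, not treatment dates.
- T1 data allow a split by status at entry, not by later change.
- The T1–T2 block shows a trend over 4 weeks, against a 6-month intervention.

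None gives treatment status at T2–T4 for every participant.

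**3. The plan's own figure.** The only stated power figure is 80 participants for about 80% power to detect a 30% increase, at a 5% type I error rate. It is not an input to this point. With 80 measured at each of two times, treated as independent and tested two-sided, 30% to 60% gives 97.4% power and 30% to 39% gives 22%. Neither reproduces 80%. The article does not state the residual variance, the sidedness, or whether the 30% is absolute or relative. The figure serves below only as a yardstick: 30 points if absolute, 0.30 × 30 = 9 points if relative.

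**4. Size of the bias.** None of these inputs is in the documents; all are assumed:

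- proportion active: 20% on treatment, 37% off, a gap of 17 points
- share on treatment at entry: 20% to 40%
- share of those who finish before T3 and reach the off-treatment rate: 25% to 100%

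As a plausibility check, 40% on treatment gives 0.4 × 20 + 0.6 × 37 = 30.2%, close to the plan's 30%. With 20% on treatment it is 0.2 × 20 + 0.8 × 37 = 33.6%.

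Apparent rise with no parkrun effect = share on treatment × share finishing × gap:

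| On treatment | Finishing | Rise (points) |
|---|---|---|
| 20% | 25% | 0.20 × 0.25 × 17 = 0.85 |
| 20% | 100% | 0.20 × 1.00 × 17 = 3.4 |
| 40% | 50% | 0.40 × 0.50 × 17 = 3.4 |
| 40% | 100% | 0.40 × 1.00 × 17 = 6.8 |

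The range is about 1 to 7 points. Against the yardstick it is 0.85/30 = 3% to 6.8/30 = 23% of an absolute effect, or 0.85/9 = 9% to 6.8/9 = 76% of a relative one.

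New treatment reverses the sign. If 5% of participants start treatment (the number finishing in the first row), the change is −0.05 × 17 = −0.85, which cancels that row.

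**5. Effect on a test.** A simulation used 80 participants, no parkrun effect, a paired T1–T3 test, and responses independent given treatment status. Activity was assumed to be 20% on treatment and 40% off, with everyone on treatment finishing. With 20% of participants on treatment the rise was 4 points, and p < 0.05 occurred in 8% of runs. With 40% on treatment the rise was 8 points, and the figure was 18%. The nominal rate is 5%. The most extreme set tried (60% on treatment, 20% against 50% active) gave 18 points and 64%. These figures depend entirely on the assumed values.

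**The case against.** The strongest reply is that the lack of a concurrent control is the root cause. The Limitations section concedes the absence of randomisation and the mix of cancer types and stages. Repeated recording would not cure this: people who finished treatment before T1 count as unchanged, yet may still be recovering. Selecting participants by later treatment change also conditions on events after entry. All of this stands, and it limits what the fix can achieve. The section does not, however, mention change in treatment status.

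A second reply is that some information will exist: missed-event follow-up, the quality-of-life questionnaire, the T3 and T4 surveys, and status at entry. That is true, so it would be wrong to say that nothing relevant is collected. These sources remain partial, for the reasons in step 2 of the working.

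A third reply is that the primary aims do not require change to be attributed to parkrun. This also stands and keeps the severity low.

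A reader might infer more than the documents support:

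- **That T1-only recording is why recovery cannot be separated from a parkrun effect.** Full separation is not available in this design even with repeated recording.
- **That treatment is the main time-varying confounder.** Nothing in the documents ranks it against others.
- **That the T2–T3 change will be read as efficacy.** No section names that contrast. The hypothesis refers to baseline, and the sample size model uses baseline, six months and follow-up.
- **That the lack of a treatment term in the described model is an error.** Covariate choice may be left to the analysis plan; the data must be collected for that choice to exist.

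**Conclusion.** The point holds in a limited form. The schedule records treatment, clinically recorded side effects and PCOC status at T1 only, in a single-arm study that mixes on-treatment and remission participants and expects treatment during the intervention. Change in treatment status after T1 therefore cannot be adjusted for when the secondary outcomes, or the activity outcome behind the sample size, are interpreted.

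The documents do not fix the size or the net direction of the bias. Under the assumed 17-point gap and the stated ranges it is an apparent rise of about 1 to 7 points, offset or reversed by new treatment or relapse. Severity is modest, because acceptability and adherence are primary.

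**What to change.** 1. At T2, T3 and T4, in contacts already scheduled, record current treatment (none or type, and date of last treatment), side effects and PCOC stage. Amend the clinical characteristics section and Table 1 to match.
2. As a sensitivity analysis, add on/off-treatment status as a time-varying covariate in the mixed models. Also report change to T3, from the same reference time point as the main analysis, in participants whose treatment status did not change.
3. State that this reduces but does not remove confounding by recovery, since there is no concurrent control, and that the unchanged-status group may include people still recovering from earlier treatment.

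The cost is a few case-report fields at three contacts, one extra model term and one extra estimate, with lower precision in the restricted group. The Experimental design section says that recruitment had not begun and no data had been collected. On that footing prospective capture is inexpensive, whereas later reconstruction would depend on recall or on medical records.

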### Outcome measures

*Physical function*: Resting heart rate, oxygen saturation (recorded using a pulse oximeter), resting blood pressure (standard auscultation), 6 min Walk Test (6MWT) and 30 s Sit-to-Stand test. These measures will be recorded at T1, T2 and T3. Participant rating of perceived effort (RPE) [29] will be recorded during and after the 6MWT and Sit-to-Stand test.*Quality of Life*: Assessed using the European Organization for Research and Treatment of Cancer (EORTC) Quality of Life Questionnaire (QLQ-30) [30]. This is a validated 30-question instrument used to assess different aspects contributing to HRQoL in cancer patients. Responses will be recorded at T1-T4.*Anxiety and depression*: Measured with the Hospital Anxiety and Depression Scale (HADS) [31]. This validated questionnaire consists of seven questions scoring levels of anxiety and seven assessing levels of depression. The scale takes approximately three to five minutes to complete and will be used at T1-T4.*GENERAL physical activity*: General physical and incidental activity, including ADL, and sitting time, will be assessed using the validated Short Form International Physical Activity Questionnaire (IPAQ-SF) [32] at T1-T4.*Dietary intake*: The Mediterranean Diet Adherence Screener (MEDAS) [33, 34] is a validated dietary assessment tool to determine adherence to a Mediterranean diet, which has been associated with improved health outcomes of cancer survivors. It consists of 14 questions (yes/no response) to assess the frequency of food groups included in the Mediterranean diet and will be administered at T1-T4.*Mood and sleep*: The Daylio Mood Diary basic version app is freely available for download to phone or smartwatch. The app allows daily diary entries for mood and sleep quality, and produces weekly and monthly graphs to track diary inputs. The app also allows participants to tap on icons that may contribute to mood and sleep quality e.g. food and water intake, stress, hobbies and leisure pursuits. These may contribute to parkrun adherence. Monthly graphs will be exported to the research team’s contact email by each participant, and data collated for each time point (T1-T4).*Participation satisfaction, diet and exercise behaviour, and intent*: A participant survey will be administered at T3 and T4. This consists of a checklist about eating and exercise behaviours, and participant feedback about the parkrun project during the study and 2-month follow up, including intent to change behaviours. The survey also includes a series of open-ended questions about parkrun where participants are encouraged to provide their opinions, likes and dislikes, levels of enjoyment, barriers to involvement, whether the intervention provided benefits and social support, and intention to continue with parkrun or other physical activity. For example, specific questions ask whether participants find parkrun fun and acceptable as rehabilitation exercise; whether it is easy to join in; did they meet new people (including other cancer survivors) and make new social connections; if they feel supported and incentivised to keep coming; if they feel safe participating; and is their quality of life improved.*Attendance and adherence*: Parkrun can provide the number of events attended by each participant through their national database, using the individual’s ID barcode number. Adherence will be calculated by dividing the number of events attended by each person by the number of available events in the 6-month period of the intervention and multiplying by 100 to give a percentage. If a participant does not finish an event, their time is not recorded.

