## Outcomes

### Study objectives

This feasibility study has been developed primarily to assess the acceptability of, and adherence to, parkrun as an enjoyable exercise intervention for cancer survivors. Secondary aims are to assess the efficacy of parkrun to improve social support, HRQoL, mental health, to prevent physical and functional decline [3, 4, 26] as well as influence dietary intake [26–28]. 

We hypothesised that:

Consistent parkrun participation will improve cancer survivor engagement in physical activity, social interaction and social identity.Cancer survivors will enjoy doing parkrun events.Parkrun participants will have improved physical function, HRQoL, mental health, disease symptoms and treatment side-effects compared to baseline measures.Parkrun participation may indirectly affect the dietary intake of cancer survivors.

Outcome measures will be assessed at enrolment and initial screening [25] (baseline, T1); after 4 weeks of usual management and activities of daily living (ADL, T2); after 6 months of parkrun participation (T3); 2 months post-intervention follow-up (T4) (Fig. 1).

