### Statistical analyses, sample size and power calculation

Numerical data from demographic, physical and scored questionnaire outcome measures will be analysed using Excel spreadsheets, IBM©SPSS version 29 and R studio [35]. Qualitative data (mood, participant feedback survey responses, participants’ attitudes towards the intervention, enjoyment, appropriateness, suitability, convenience and perceived effectiveness of the intervention) will be analysed thematically using NVivo and following the process of Braun and Clarke (2006) [36]. Comments will be read, organised and coded using an iterative framework (familiarisation; generation of initial codes; search for themes; review of themes; definition of themes and a final report). The codes will be reviewed, discussed and refined with the coding framework drawn from the data as well as being informed by the survey questions and themes highlighted in wider literature on parkrun outcomes [19, 20]. 

Participant demographic and cancer-related variables will be summarised using descriptive statistics (e.g. count or percent; mean and standard deviation). Linear mixed effect models will be used to determine the effect of parkrun participation on the proportion of participants meeting minimal PA recommendations. These models will include a random intercept for each participant, to account for the clustering of observation on each individual (i.e. measurements at baseline, 4-weeks usual activities, following 6 months of parkrun participation, and 2-month follow-up). A histogram and quantile-quantile plot of the model residuals will be used to determine whether the assumption of normally distributed errors is met. Model fit will be assessed using the adjusted R^2^ value and the model residual standard error; the most parsimonious model will be selected for inferences. Effect sizes (Cohen’s d) will be calculated where there are significant effects of time using the pooled standard deviation as the denominator.

In the case of participant attrition from the study, or if participants miss parkrun events in the 6-month intervention period, researchers will follow up with each participant individually, either through the study or at the end of the study. Reasons for reduced attendance or attrition can be gained from the participant and this information is valuable for informing the researchers of potential barriers or issues with parkrun as a mode of cancer rehabilitation exercise.

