Sample size was determined via simulation methods using a random intercept model with the R package [35]. We were interested in powering the study to detect changes in exercise adherence (measured as the proportion of cancer patients meeting minimum physical activity guidelines) and used this outcome variable in simulations. Data used to create the model were informed by previous studies [8, 10]. We assumed the average proportion of cancer patients meeting minimal physical activity guidelines for aerobic exercise was 30% [37]. Time (three levels- baseline, 6-months parkrun and follow-up), body mass index (BMI) and sex (two levels- male and female) were included as fixed factors within the sample size model. A random intercept was included for each individual participant. BMI and sex were included as fixed factors as these variables can influence exercise adherence in cancer patients [8–10]. Calculations were made assuming fixed effects of 6%, 30% and 5% for sex, time and BMI respectively, and a standard deviation of the random intercept of 2%. Based on these assumptions and a type I error rate of 5%, 80 participants give approximately 80% power to detect the specific time effect of 30% increase in the proportion of participants meeting physical activity recommendations. A minimum of 100 participants will be recruited, which even allowing for potential attrition of 20 participants would still provide a minimum sample size of 80.

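### The acceptability survey is scheduled only at T3 and T4, and early leavers are not stated to receive its items, so the acceptability result may be over-favourable

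*Protocol article*

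**What the plan says.** The Study objectives section of the protocol article states that the study was "developed primarily to assess the acceptability of, and adherence to, parkrun as an enjoyable exercise intervention for cancer survivors". The abstract likewise names acceptability and adherence as the primary objectives.

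Under Outcome measures, acceptability is asked about in the participant survey: "specific questions ask whether participants find parkrun fun and acceptable as rehabilitation exercise". On timing, the same paragraph says "A participant survey will be administered at T3 and T4". Table 1 agrees: its row "Participant Satisfaction, Diet, Exercise behaviour, Intent Feedback Surveys" is marked at T3 and T4 and nowhere else.

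The statistical section deals with people who drop out or miss events. Researchers will contact each of them individually, during the study or at its end, and "Reasons for reduced attendance or attrition can be gained from the participant". The stated use is to learn about barriers to parkrun as rehabilitation exercise. Survey responses, attitudes and enjoyment "will be analysed thematically using NVivo".

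The sample-size paragraph allows for losses: "potential attrition of 20 participants would still provide a minimum sample size of 80".

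**The concern.** T3 follows a 4-week control period and a 6-month parkrun block, so acceptability is first asked about roughly 7 months after enrolment. Participants may withdraw at any time. Anyone who leaves the study before T3 has, on the stated schedule, no planned occasion on which to answer the acceptability and enjoyment questions. The contact planned with leavers gathers reasons for leaving, which is related information but not the same items. The article does not say that what they report joins the acceptability analysis.

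Leaving can itself be a sign that parkrun did not suit someone, so non-response may be related to the answer. The other primary outcome is less exposed: adherence is counted from parkrun's own database and does not depend on completing a survey.

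What is at stake is one of the two things the study exists to assess, and the article says the trial should lead to a larger longitudinal study. This is also a matter of data collection. A later analysis plan can choose a denominator, but it cannot recover answers that were never asked for.

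**Working it through.** **Inputs from the article.** 100 recruited; 20 losses allowed for (sample-size paragraph); survey at T3 and T4 only (Outcome measures and Table 1).

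**Inputs assumed, because the article gives no acceptability rate.** Favourable share among stayers, a_s: 70% to 90%. Favourable share among leavers, a_l: 20% to 80%. For the illustration, all 20 losses occur before T3, none of them is surveyed, and all 80 stayers respond.

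**Step 1: the article's own figure.** 100 − 20 = 80, and 80 / (1 − 0.20) = 100. The allowance reproduces. The share surveyed is r = 80/100 = 0.80.

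**Step 2: bounds for all enrolled.** Lower bound = r × a_s (no leaver favourable). Upper bound = r × a_s + (1 − r) (every leaver favourable). The width is 1 − r = 0.20, or 20 points, whatever a_s is.

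- a_s = 70%: 0.80 × 0.70 = 56%, up to 76%.
- a_s = 80%: 0.80 × 0.80 = 64%, up to 84%.
- a_s = 90%: 0.80 × 0.90 = 72%, up to 92%.

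With 10% lost the width would be 10 points; with 30% lost, 30 points.

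**Step 3: difference between the stayers' figure and the all-enrolled figure.** Bias = (1 − r) × (a_s − a_l) = 0.20 × (a_s − a_l), in percentage points:

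| Stayers favourable | Leavers 20% | Leavers 50% | Leavers 80% |
|---|---|---|---|
| 70% | +10 | +4 | −2 |
| 80% | +12 | +6 | 0 |
| 90% | +14 | +8 | +2 |

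The bias is upward only if leavers are less favourable than stayers. It is zero if they agree and slightly negative if leavers are more favourable.

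**Step 4: comparison with sampling error.** With 72 of 80 favourable (90%), the Wilson 95% interval is 81.5% to 94.8%, which is 13.3 points wide with a half-width of about 7 points. The 20-point range from unsurveyed leavers is wider than that interval. If half of the leavers were favourable, the bias of 8 points would be about the size of the half-width.

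**The case against.** The strongest reply has five parts.

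- **No acceptability percentage is planned.** Responses are analysed thematically, and no numerical target or denominator is set. This stands, and the percentages above are illustrations only. It does not remove the problem, because themes drawn mainly from stayers are selected in the same way.
- **Leavers are not barred from the survey, and stopping parkrun is not leaving the study.** Attendance is at each participant's discretion, so someone who dislikes parkrun can stop going, stay enrolled and still be surveyed at T3. This stands and narrows the gap to people lost to the study. For them the article makes no stated provision.
- **Leavers are already contacted about barriers.** This is a real partial safeguard, particularly for a qualitative outcome. It is loosely worded, however, and has no stated link to the acceptability items or result.
- **People may leave for reasons unrelated to parkrun.** For missed events the article anticipates treatment cycles, symptoms, family, work and weather. Losses of that kind need not depend on the acceptability answer, so the direction of bias is plausible rather than established.
- **Denominators and sensitivity analyses belong in an analysis plan.** That is fair for those details, and neither the full protocol nor an analysis plan is shown. The timing of the survey, by contrast, is fixed in this document.

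A reader might go further and infer that the trial will publish an acceptability figure for completers alone, overstated by as much as 18 points: 90% − 72%, or 0.20 × (0.90 − 0). The documents do not support this. It needs an assumed 90% among stayers, all 20 losses (an allowance, not a forecast), and no favourable answer from any leaver, applied to a percentage the article never defines.

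**Conclusion.** The point holds in a limited form. The survey that carries a primary objective is scheduled only at T3 and T4. People who leave the study earlier are followed up for reasons, but they are not stated to receive the acceptability and enjoyment items or to be counted in the result. The acceptability result may therefore be over-favourable.

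Size and direction cannot be derived from the document. What can be said is that, if the full allowance of 20 in 100 goes unsurveyed, any all-enrolled proportion is uncertain by 20 points. The 72% to 92% example rests on the assumed 90% among stayers. Upward bias rests on the further assumption that leavers are less favourable than stayers. The change is worth making because it is cheap and concerns a primary outcome.

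**What to change.** At the individual contact already planned for people who withdraw, give the T3 survey's acceptability and enjoyment items once. State that these answers, together with the reasons for leaving, are included in the acceptability analysis, and report how many of all enrolled participants contributed. If an acceptability percentage is reported, show it for respondents and, beside it, best-case and worst-case bounds for all enrolled.

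Two stronger measures are not needed. Asking the items after every missed event would mean repeated administration at irregular times, since the article expects many participants to miss weeks. Counting every non-responder as finding parkrun unacceptable presupposes a yes/no endpoint that the article does not set; the bounds already show that extreme.

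The cost is a few existing questions added to an existing contact, one line of reporting, and possibly a less favourable result. The article says recruitment was about to start, so the change is best made before early leavers are lost to contact.
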